**Methods: Assignment of interventions (for controlled trials)**

**16a. Allocation: Sequence generation**

The randomization process was centrally performed with a 2:1 ratio to intervention and control groups.

The allocation sequence will be generated using computer-based random number generation. No stratification factors are planned due to the pilot nature of the study.

**16b. Allocation concealment mechanism**

The allocation sequence will be concealed using a centralized assignment system, and the allocation will not be revealed to participants until enrollment is confirmed.

**16c. Implementation**

The allocation sequence will be generated by a member of the research team not involved in recruitment. Clinical investigators at HGUGM will enroll participants and assign them to study arms.

**Blinding (masking)**

**17a. Who will be blinded**

This is an open-label study due to the nature of the intervention. Patients, investigators, and clinical research coordinators will be aware of the allocation. No blinding is applied.

**17b. Unblinding procedure**

Not applicable, as the study is not blinded.

**Methods: Data collection, management, and analysis**

**18a. Data collection methods**

Baseline, outcome, and follow-up data are collected through validated questionnaires, physical assessments, laboratory tests, and biomarker analyses.
Data quality is promoted through validated instruments and pseudonymization. Assessment tools include EuroQoL-5D, FACIT-Fatigue, IPAQ, HADS, PANAS, etc.; their reliability/validity is referenced.

**18b. Participant retention and follow-up**

Follow-up assessments are scheduled at the end of the 12-week intervention and 6 and 12 months. To promote retention, regular contact and reminders will be used. If a participant discontinues the intervention, efforts will be made to collect primary outcome data at scheduled time points.

**19. Data management**

Patient data are pseudonymized using alphanumeric codes. HGUGM and Ejercicio y Cancer conduct data collection, entry, cleaning, and monitoring. PROs are collected electronically. The protocol refers to compliance with Spanish data protection law and EU GDPR.

**20a. Statistical methods for main outcomes**

Descriptive statistics will be used. Kruskal-Wallis tests and multiple regression models will assess the impact of the intervention on weight and body composition.
Software: Stata v15 and SPSS v29.

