- Histologically confirmed HR-positive stage I to III invasive BC.
- Premenopausal status clinically defined as a patient who maintains menstruation prior to chemotherapy initiation if his has taken place and/or regular menstruation at the time of consent.
- Completed locoregional treatment (surgery and radiotherapy).
- Ongoing adjuvant treatment including OFS drugs expected to be maintained for at least 4 months at the time of consent.
- Functional status by the Eastern Cooperative Oncology Group (ECOG) scale 0-1.
- Ability to understand and give informed consent (IC).

Exclusion criteria

- Any medical contraindication to exercise practice.
- Any American Thoracic Society (ATS) contraindications for cardiopulmonary exercise testing^1^ .
- Active metastatic BC or other concurrent cancer diagnosis at the time of consent.
- Pregnant or breastfeeding women.
- Alcohol or other drugs abuse (excluding smoking) defined as a pattern of usual consumption that results in physical, mental or social functioning impairment.
- Any condition that makes the patient ineligible based on the investigator’s criteria.

1. **Study Type**
   - Type of study: Interventional study.
   - Study design including:
     - Method of allocation: Randomized study.
     - Masking: open-label study.
     - Assignment: two arms, crossover assignment allowed according to patient choice after the 2^nd^ follow-up time point.
     - Purpose: Treatment
   - Phase (if applicable): pilot study.
2. **Date of first enrollment:** August 2024
3. **Sample Size**

The trial was planned to enroll 30 patients.

Finally, participants enrolled were 27: 3. Patients did retire informed consent after being enrolled.

1. **Recruitment status:** Complete.
2. **Primary Outcome(s):** See section 12 SPIRIT checklist below.

Impact of the combined intervention on weight and body composition: This endpoint will be assessed by the following variables: weight, height, body mass index (IMC), waist and hip circumferences, waist-to-hip ratio (WHR), fat mass, lean mass and extracellular water which will be obtained with Tanita BC-601 Gold weight scale and bioelectrical impedance analysis as well as a measuring tape.

Timepoints of primary interest: Primary outcomes will be assessed immediately before the 12-week intervention period and at the end of it.

1. **Key Secondary Outcomes:** See section 12 SPIRIT checklist below.

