Finally, nutritional and psychological status are also included as secondary endpoints. Nutritional status will be assessed by a 3-day nutritional record, PREDIMED Mediterranean Diet Adherence Score^7^ and compliance with WCRF/AICR cancer prevention recommendations^8,9^. Positive and negative affect scale (PANAS)^10^, transtheoretical model of physical activity change questionnaire^11,12^ and MOS social support survey^13,14^ will serve to evaluate psychological status.

Primary and secondary endpoints will be assessed immediately before the 12-week intervention period and at the end of it. They will be also evaluated at 6- and 12-months follow up timepoints.

Exploratory endpoints: Chronic inflammation has been linked to cancer development^39^. On the other hand, skeletal muscle acts as an endocrine organ whose contraction releases myokines (cytokines or peptides); exercise-induced myokines can exert an anti-inflammatory action^40^. The biomarker test proposed for this study aims to evaluate the potential impact of the combined intervention on pro-inflammatory markers (C-reactive protein (CRP), tumor necrosis factor alpha (TNF-α)), anti-inflammatory markers (adiponectin^27^) and oncostatin-M (multifunctional myokine that has been related to apoptosis simulation in BC cell lines^38^).

Exploratory endpoints will be assessed immediately before the 12-week intervention period and at the end of it.

1. **Participant timeline**

The following figure summarizes the study assessments from enrolment. We define week 1 to 3 as the moment in which patients are enrolled at HGUGM BC unit and we collect demographic information. Initial and final assessments take place the week before and after the 12-week intervention period (week 4 and 17), respectively. Blood for secondary endpoints and biomarker analysis is collected on week 4 and 17. On week 40 and 64, 6 and 12 months after the 12-week intervention respectively, a new general assessment (physical, nutritional and psycho-oncological evaluation) along with blood collection for secondary endpoints take place.

[figure not shown]

1. **Sample size**

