**20b. Additional analyses**

The Nonparametric Kruskal-Wallis test will also be used for secondary endpoints and biomarker analysis. No mention of subgroup or adjusted analyses.

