**20c. Analysis of population and handling of missing data**

The primary analysis will follow the intention-to-treat principle. If feasible, missing data will be addressed using appropriate imputation methods, such as multiple imputation.

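### Secondary and biomarker outcomes get only a covariate-free rank test, and the primary analysis names a rank test and a regression without making a baseline-adjusted model the lead

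*Protocol*

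**What the plan says.** Section 20a covers weight and body composition: "Kruskal-Wallis tests and multiple regression models will assess the impact of the intervention on weight and body composition". It does not rank the two methods. It also does not say whether the rank test uses week-17 values or changes, or which covariates enter the regression.

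Section 20b covers the rest: "The Nonparametric Kruskal-Wallis test will also be used for secondary endpoints and biomarker analysis". It then adds: "No mention of subgroup or adjusted analyses".

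Section 20c sets an intention-to-treat analysis and says: "If feasible, missing data will be addressed using appropriate imputation methods, such as multiple imputation".

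On timing, the Outcomes section says: "Primary and secondary endpoints will be assessed immediately before the 12-week intervention period and at the end of it". It schedules the exploratory biomarkers at the same two points. The Participant timeline places these assessments at weeks 4 and 17.

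On size, the registration data at the front of the protocol say "The trial was planned to enroll 30 patients" and then "Finally, participants enrolled were 27: 3. Patients did retire informed consent after being enrolled". Section 16a says "The randomization process was centrally performed with a 2:1 ratio to intervention and control groups" and plans no stratification. The Sample size section says that no earlier data allowed an expected difference between arms to be set.

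**The concern.** A Kruskal-Wallis test on two arms is the rank-sum test. It has no place for a covariate, and its output is a p-value. For secondary endpoints and biomarkers it is the only test named, so as written the protocol provides no adjusted difference and no interval for them. It also sits poorly with section 20c: the usual rules for combining multiply imputed data sets pool an estimate and its standard error, and this test supplies neither.

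For the primary outcome the regression could supply both, but nothing commits it to the baseline value or puts it ahead of the rank test.

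Two things are at stake. The first is precision in a trial of 27 patients, where baseline should predict follow-up strongly for outcomes such as weight. The second is the product of the pilot. Since the protocol says no prior difference was available, an estimate with its interval is the most useful thing a later trial could take from this one.

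**Working it through.** The protocol gives no alpha, power, effect size, standard deviation or correlation, and 30 is a recruitment estimate, so there is no calculated figure to reproduce. The one check available is 30 − 3 = 27.

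**Inputs from the protocol.** N = 27; allocation 2:1; outcomes measured before and after the intervention.

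**Assumptions.** An 18:9 split (the actual split is not given); two-sided alpha 0.05; equal variances; a correlation r between the week-4 and week-17 values, varied from 0.5 to 0.95.

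**Chance imbalance.** The standard error of a baseline difference between arms is √(1/18 + 1/9) = 0.408 SD. The probability of a difference above 0.5 SD in either direction is 2 × [1 − Φ(0.5/0.408)], about 22%.

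**Residual variance, in units of the outcome variance.**
- Week-17 value, unadjusted: 1
- Change from baseline: 2(1 − r)
- ANCOVA: 1 − r²

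The ratio of ANCOVA to change is therefore (1 + r)/2.

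**95% interval half-width.** Unadjusted: t(25 df) × 0.408 = 0.84 SD. Change: the same × √[2(1 − r)]. ANCOVA: t(24 df) × 0.408 × √(1 − r²) × √(1 + 1/23), where the last factor is the expected cost of chance imbalance in the covariate.

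| r | ANCOVA / week-17 variance | 27 patients act like (27 ÷ ratio) | ANCOVA / change variance | Half-width, SD: week-17 / change / ANCOVA |
|---|---|---|---|---|
| 0.5 | 0.75 | 36 | 0.75 | 0.84 / 0.84 / 0.75 |
| 0.8 | 0.36 | 75 | 0.90 | 0.84 / 0.53 / 0.52 |
| 0.9 | 0.19 | 142 | 0.95 | 0.84 / 0.38 / 0.38 |
| 0.95 | 0.10 | 277 | 0.975 | 0.84 / 0.27 / 0.27 |

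The variance ratios and equivalent sample sizes leave out the 1/23 term; the half-widths include it.

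**Simulated power** at a true difference of 0.5 SD (4,000 runs per setting, normal data):

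| r | Kruskal-Wallis, week-17 | Kruskal-Wallis, change | ANCOVA |
|---|---|---|---|
| 0.5 | 0.19 | 0.21 | 0.27 |
| 0.8 | 0.20 | 0.43 | 0.48 |
| 0.9 | 0.20 | 0.72 | 0.75 |
| 0.95 | 0.19 | 0.95 | 0.95 |

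With no true difference, all three rejected in about 4% to 6% of runs. The gain of ANCOVA over the rank test on change runs from 0.7 points (0.948 to 0.955 at r = 0.95) to 6.1 points (0.206 to 0.267 at r = 0.5).

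**The case against.** The strongest reply is that section 20a already names multiple regression, which gives a coefficient with an interval and can include baseline. The choice of covariates, response form and lead method is often left to a statistical analysis plan, which is not at hand here. This stands in part. A reader might infer that the primary analysis ignores baseline and yields no effect estimate; the text does not support that for weight and body composition. But the reply does not reach section 20b, which positively names one test for secondary endpoints and biomarkers. A later plan that used an adjusted model there would depart from the protocol.

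The remark in 20b about adjusted analyses reads like a drafting note and is weak evidence about the regression in 20a. The point does not depend on it.

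A reader might also infer that adjustment would always be far more precise. That holds only if the rank test is run on week-17 values and the correlation is about 0.8 or higher. The protocol does not say which values are meant, and on change scores most of the gain disappears.

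Nor does chance imbalance make the unadjusted test wrong. Under randomisation it keeps its error rate, as the simulation shows; the loss is of power. A rank test would be invalid for comparing before and after values within the same patients, but the trial design section defines the comparison as between arms, so that misuse is hypothetical.

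On imputation, section 20c is conditional, and regression estimates can be pooled. The mismatch therefore bites mainly on the outcomes given Kruskal-Wallis alone.

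Finally, a Hodges-Lehmann shift with an interval could accompany a rank-sum test. The protocol names none, and it would still be unadjusted.

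**Conclusion.** The point holds as a choice of method that can be improved, not as an error of validity. For secondary endpoints and biomarkers, the protocol fixes a test that cannot use the scheduled baseline as a covariate and by itself gives no estimate. For the primary outcome, it leaves the better method unranked and unspecified.

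Compared with an unadjusted test of week-17 values, ANCOVA reduces residual variance by about 25%, 64%, 81% or 90% at correlations of 0.5, 0.8, 0.9 or 0.95. Compared with a rank test on change, the gain is about 1 to 6 power points, and the benefit is mainly the adjusted difference with its interval.

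These sizes rest on an assumed 18:9 split, assumed correlations and roughly normal data. They also assume that baseline was in fact recorded: the protocol schedules it for every patient but does not show that it is complete.

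**What to change.** In section 20a, name one primary analysis: a linear model of the week-17 value on arm and the week-4 value, reported as the adjusted difference between arms with its 95% confidence interval. In section 20b, use the same model for continuous secondary and biomarker outcomes, on the log scale where they are skewed. Keep Kruskal-Wallis on change from baseline as a sensitivity analysis. If multiple imputation is used, pool the adjusted difference.

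A mixed model over weeks 4, 17, 40 and 64 is not needed for this and brings problems. Biomarkers are scheduled only at weeks 4 and 17. The Study Type entry allows crossover after the second follow-up time point, while section 6b and the trial design section place it after the last follow-up analysis. Unless those passages are reconciled, later visits might include controls who have crossed over.

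The cost is wording, and the stated software (Stata and SPSS) can fit the model. Residual normality must be checked, which the rank sensitivity analysis covers. Because the trial is open-label and recruitment is complete, the change should be fixed and dated before the outcome data are analysed, so that it cannot be taken for a choice made after seeing results.

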**20b. Additional analyses**

The Nonparametric Kruskal-Wallis test will also be used for secondary endpoints and biomarker analysis. No mention of subgroup or adjusted analyses.

**20c. Analysis of population and handling of missing data**

The primary analysis will follow the intention-to-treat principle. If feasible, missing data will be addressed using appropriate imputation methods, such as multiple imputation.

**Methods: Monitoring**

**21a. Data Monitoring Committee (DMC)**

Due to the pilot nature and low risk of the intervention, a data monitoring committee has not been established.

**21b. Interim analyses and stopping guidelines**

No interim analyses or formal stopping rules are planned for this pilot study.

**22. Harms**

Adverse events will be evaluated and graded using CTCAE v5.0. The study assesses a broad set of therapy-associated adverse events.

**23. Auditing**

No independent auditing is planned. Data quality will be internally monitored by study coordinators.

**Ethics and dissemination**

**24. Research ethics approval**

Approved by the HGUGM Drug Research Ethics Committee (CEIm). Protocol complies with the Declaration of Helsinki.

1. **Protocol amendments**

Relevant protocol amendments will be communicated to investigators, the CEIm, participants (as needed), and updated in the clinical trial registry.

**26a. Informed consent**

Eligible patients provide written informed consent before any procedure.

**26b. Additional consent for ancillary studies**

No additional consent for ancillary studies involving biological specimens is currently planned.

1. **Confidentiality**

Personal data are pseudonymized. Only investigators have access to identifiable data. Compliance with Spanish and EU data protection laws.

1. **Declaration of interests**

All authors declare no competing financial or personal interests.

1. **Access to data**

Access to the final dataset will be restricted to study investigators. No contractual agreements limiting access are reported.

**30. Ancillary and post-trial care**

No specific provisions for post-trial care or compensation for trial-related harm are included, given the low-risk nature of the intervention.

**31a. Dissemination policy**

Results will be presented at scientific conferences and published in peer-reviewed journals.

**31b. Authorship eligibility**

Authorship will be decided by the PIs based on substantial contributions to study design, conduct, analysis, or manuscript writing, following ICMJE criteria.

**31c. Public access to data and protocol**

There are currently no plans to grant public access to the full protocol, participant-level dataset, or statistical code.

**Appendices**

1. **Informed consent materials**

Attach the model consent form as an appendix for submission.

1. **Biological specimens**

Blood samples will be collected to analyze inflammatory markers (CRP, TNF-α, adiponectin, oncostatin-M).

Storage and evaluation details are not fully described.
*Suggested text:* Biological specimens will be processed and stored according to standard operating procedures at HGUGM laboratories for biomarker analysis.

